#### Primary outcome measures–lower limb joint reaction forces

Internal joint loading of the hip, knee and ankle (i.e., joint reaction forces, ‘N’) will be estimated by means of an optimal control framework (see *“Planned Data Analysis”*) using a direct collocation data-tracking method, derived from the collected experimental kinetic, kinematic, muscle activation and muscle-tendon unit behaviour data (*“Secondary Outcome Measures–Experimental Data”*, Table 4).

#### Secondary outcome measures–experimental data

*Kinetics*. Ground reaction forces (‘N’) extracted from the force instrumented treadmill will be collected, providing data on external forces acting on participants during movement.

Using OpenSim’s [59, 60] inverse dynamics algorithms, net joint forces (‘N’) and net joint moments (‘N·m’) of the hip, knee and ankle will be determined for each dynamic trial.

*Kinematics*. Single and double support phases (percentage of the gait cycle, ‘%’), stride length (‘m’) and frequency (‘Hz’) of the locomotion trials will be determined, in addition flight and contact times (seconds, ‘s’) will be collected for the running, skipping and plyometric trials.

Using OpenSim’s [59, 60] inverse kinematics algorithms, the posture (i.e., positions and angles of the degrees of freedom, ‘m’ or ‘°’) and velocities (i.e., the time derivative of the positions and angles, ‘m·s^-1^’ or ‘°·s^-1^’, respectively) will be determined for each dynamic trial.

*Muscle-tendon unit behaviour*. Muscle-tendon unit behaviour of the m. gastrocnemius medialis will be modelled by determining the activation, geometries–muscle length (i.e., length of the contractile element, ‘mm’), tendon length (i.e., length of the series elastic component, ‘mm’), and pennation angle (i.e., the angle between the fascicle and the deep aponeurosis, ‘°’)–, and forces–tendon force (i.e., force directed along the series elastic component, ‘N’), muscle force (i.e., the summed forces from the contractile and parallel elastic components, ‘N’)–, using Hill-type muscle model formulations [61] (see *“Planned Data Analysis”*).

Additionally, muscle contraction dynamics of the m. gastrocnemius medialis will be determined through ultrasonography, measuring tendon strain (i.e., the change in distance between the myotendinous junction and the osteotendinous insertion represented by the midpoint of the medial and lateral calcaneus markers, ‘mm’), muscle fascicle length (i.e., the distance between the insertion of the fascicles into the superficial and the deep aponeuroses, ‘mm’), pennation angle (i.e., the angle between the fascicle and the deep aponeurosis, ‘°’), and fascicle velocity (i.e., the time derivative of the fascicle length, ‘mm·s^-1^’). In addition, changes in fascicle length, changes in pennation angle, a modified version of the architectural gear ratio [62, 63], as well as m. gastrocnemius and m. soleus pre-activations [64] will be analysed.

Furthermore, muscle activation dynamics of m. gluteus maximus, m. rectus femoris, m. vastus lateralis, m. biceps femoris (lateral hamstrings), m. semitendinosus (medial hamstrings), m. tibialis anterior, m. gastrocnemius and m. soleus will be collected bilaterally.

### Planned data analysis

All collected experimental data will be used as input into an optimal control framework (Fig 3). This framework uses a direct collocation method to track experimental kinematics, net joint moments, and ground reaction forces for a single movement cycle. A movement cycle is defined as two successive contacts of the right foot (e.g., a stride) for the locomotion trials, and one contact and subsequent flight phase for the plyometric movements. The goal of the simulation is to minimise the cost function, consisting of a muscle-sharing term, data tracking terms and control variable minimisation terms, to estimate muscle activations for a given moment in time. The framework is thus designed to elicit a dynamically consistent simulation through tracking experimental data, whilst simulating joint reaction forces.

**Fig 3 pone.0278051.g003:**
[figure not shown]
A schematic of the data workflow to obtain the main outcome measure, joint reaction forces. Experimental data are fed into the direct collocation optimal control framework to perform data-tracking simulations. Experimental EMG and ultrasound data are compared to simulated muscle-tendon unit (MTU) activations and behaviour, respectively, to validate the simulated MTU outcomes. The MTU outcomes are then used to inform a joint reaction analysis to calculate the joint reaction forces as a function of simulated kinematics, external loads (ground reaction and support forces), and MTU forces. EMG = electromyography.

#### The musculoskeletal model

A generic OpenSim (Simbios, Stanford, California, USA [59, 60]) musculoskeletal model that has been validated for high knee flexion movement will be used within the framework (Fig 4, Lai *et al*. 2017 [65]). Skeletal motion within the framework is modelled with Newtonian rigid body mechanics and Hunt-Crossley foot-ground contacts. The model consists of 23-segments–ground, pelvis, torso, and, bilaterally, femur, patella, tibia-fibula, talus, calcaneus, toe, humerus, radius, ulna, and hand–with 37 degrees of freedom (DOF). Pelvis translation and rotation with respect to the ground will be modelled as a six DOF joint. The torso-pelvis, shoulder, and hip joints will be modelled as three DOF ball-and-socket joints, the wrists as two DOF universal joints, whilst ankle, subtalar, elbow, radioulnar and metatarsophalangeal (MTP) joints as single DOF hinge joints. The MTP and wrist joints will be locked at 0°. The tibiofemoral joint (knee) will be modelled as a single DOF hinge joint, with a 0–140° flexion range. The remaining tibia rotations and translations relative to the femur, and the sagittal plane patellofemoral joint motion (i.e., anteroposterior and vertical translation, and rotation about the mediolateral axis), will be defined by polynomials as a function of knee flexion.

**Fig 4 pone.0278051.g004:**
[figure not shown]
The OpenSim musculoskeletal model that will be used for the analysis (Lai et al. 2017 [65]). Red elements represent the muscle-tendon units, pink spheres represent marker placements on the participant.

The hip, knee, ankle, and subtalar DOF will be actuated by 80 Hill-type MTU, with the toes, torso and upper body driven by 19 ideal torque actuators. Idealised torques driving the non-muscle actuated DOF will be described as a function of activation and maximum torque. The foot-ground interactions will be modelled with six-spheres per foot–four attached to the calcaneus and two to the toe segments. Hunt-Crossley equations, modified to be double continuously differentiable [66], will be used to calculate the forces at each of the six spheres.

The generic musculoskeletal model will be linearly scaled within OpenSim. Dimension-specific scale factors per body segment will be determined by identifying the 3D distance between pairs of anatomical markers and by calculating the ratio between the experimental and modelled distances. These scale factors will be used to scale anthropometrics (i.e., segment length, width and depth), and inertial parameters (i.e., segment masses and moments of inertia) to each participant. A combination of automatic and manual scaling methods is used to scale muscle-tendon unit model parameters (see *“Muscle-Tendon Unit Modelling”*).

*Muscle-tendon unit modelling*. Three-element Hill-type muscle model formulations will be used in this framework [61, 67, 68]. Briefly, the MTU complex consists of a contractile component, a passive elastic component parallel to the contractile component, and a series passive elastic component. Active (force-length and force-velocity) and passive (parallel and series) force generation are modelled via the dimensionless equations presented by De Groote *et al*., [69]. The parameters maximum isometric force, optimum fibre length, pennation angle at optimum fibre length, maximum shortening velocity, and tendon slack length are used to describe the dimensionless formulations. The MTU parameters will be scaled based on the participant’s anthropometrics (i.e., segment length, width and depth). Total MTU lengths will be adjusted during scaling such that the ratio of optimal fibre length to tendon slack length is maintained.

Maximum isometric force will be updated by estimating physiological cross-sectional area from muscle volumes calculated as a function of participant height and mass [70] and the scaled optimal fibre lengths. Physiological cross-sectional area will then be multiplied by specific tension (60 N/cm^2^), as performed previously [71]. Maximum shortening velocities are set to ten times the optimal fibre lengths [72]. Pennation angles at optimum fibre length from the unscaled model will be retained. Lengths, shortening velocities, and moment arms of MTUs will be defined as a function of joint positions and velocities [72, 73]. Polynomial coefficients will be determined for muscle lengths, velocities and moment arms, extracted using OpenSim’s Muscle Analysis with the model positioned across a range of motion that exceeds the expected experimental data. Excitation-activation dynamics of the MTUs will be modelled via Raasch’s activation model [74]–with modifications by De Groote *et al*., [61].

#### Optimal control framework

The framework (Fig 3) will be formulated as optimal control problems (OCP) and will be implemented in MATLAB (Mathworks INC., USA) using CasADi (OPTEC, KU Leuven, Belgium [75]) and a modified version of OpenSim [59, 60] and SimBody (Simbios, Stanford, California, USA [76]) to allow for algorithmic differentiation. Algorithmic differentiation (AD) allows for efficient and truncation-free evaluation of derivatives required by a non-linear program (NLP), which can lead to an almost 20-fold decrease in required simulation processing time [77].

Foot-ground contact sphere stiffness and damping (constant across all spheres) and their 3D position will be included as static parameters within the optimisation (p_cm_). The remaining parameters (i.e., sphere radii, frictions, and transition velocity) will be kept constant. The state (x) and control (u) variables will be selected to allow efficient numerical formulation of the musculoskeletal system. The skeletal dynamics of the state variables, q and $\dot{q}$, which correspond to the positions and velocities of each DOF, respectively, will be imposed by the DOF accelerations, $\ddot{q}$. Muscle activations, a_MA_, and normalised tendon forces, F_t_, are introduced to describe the MTU state, with their first time derivatives, ${\dot{a}}_{MA}$ and ${\dot{F}}_{t}$, introduced as control variables to impose activation and contraction dynamics, respectively [69]. The states of idealised torque actuators will be described by their activations, a_TA_, and controlled by their excitation, e_TA_. Control variables will be introduced for the ground reaction forces, u_GRF_, as performed previously [66]. This process will improve the convergence rate as the foot-ground contact sphere forces are subject to large fluctuations for small adjustments to the skeletal kinematics. Reserve actuators will be added to muscle-driven DOF as control variables, u_res_, that describe the instantaneous moment being produced, to help convergence of the data tracking simulations.

The objective function will be formulated to minimise muscular effort and error between simulated and experimental data to promote physiologically realistic simulations. For instance, muscle-sharing (co-activation) will be achieved through minimisation of the summed muscle activations squared. Squared activations will be weighted by muscle volume to replicate a minimisation of muscular effort simulation [78]. This approach has been successfully used in submaximal [79] and maximal voluntary effort simulations [80] and is deemed appropriate for all the movements defined in our protocol. Data-tracking terms will be formulated as the squared error between experimental and simulated data for kinematics (angles and positions), ground reaction forces, and net joint moments. Tracking terms will be scaled to ensure terms are numerically similar within the objective function. Minimising the sum of squared terms will be included for reserve actuators and control variables ($\ddot{q}$, ${\dot{a}}_{MA}$, ${\dot{F}}_{t}$) [72, 80]. Each term will be weighted, determined via manual tuning, to achieve accurate data-tracking and physiologically realistic simulations. The validity of the simulations MTU activations and behaviour will be assessed through comparison with the experimental EMG and ultrasound data. The objective function, including term weightings, will be kept constant once calibrated.

Each OCP will be transcribed into NLP via a direct collocation method and solved using IPOPT [81]. Foot-ground contact model parameters will be included as static parameters¸ p = [p_CM_]. Initially, the state (x = [q, $\dot{q}$, a_MA_, F_t_, a_TA_]) and control (u = [$\ddot{q}$, ${\dot{a}}_{MA}$, ${\dot{F}}_{t}$, u_GRF_, e_TA_]) trajectories will be discretised across 50 equally spaced mesh points between the start and end of the movement cycle [78]. The number of mesh intervals will be reassessed and adjusted accordingly once data have been collected. The state trajectories will be further discretised into three-point intervals (collocation points) between mesh points using Legendre-Gauss-Radau quadrature and approximated with third-order polynomials. Net joint forces and moments via inverse dynamics, and Hunt-Crossley forces will be estimated at each mesh point as a function of the model’s kinematics (i.e., q, $\dot{q}$, $\ddot{q}$), external forces (i.e., u_GRF_ and body weight support forces), and foot-ground contact model parameters (i.e., p_cm_). State, control and static variables will be bounded and then scaled within the NLP such that each variable falls within the interval -1 to 1 to improve the numerical conditioning of the NLPs [82].

A series of dynamic constraints will be imposed at each collocation point to maintain system dynamics. The skeletal dynamics and activation dynamics will be imposed as implicit constraints via first-order differential equations (e.g., dq/dt - $\dot{q}$ = 0, $d\dot{q}/\mathrm{dt}$ - $\ddot{q}$ = 0, da_MA_/dt– ${\dot{a}}_{MA}$ = 0, dF_t_/dt– ${\dot{F}}_{t}$ = 0). Explicit constraints will be imposed on the excitation-activation dynamics of the idealised torque actuators as the time delay between excitation and activation [72]. Path constraints are imposed at the beginning of each interval to achieve physiologically appropriate solutions. The muscle forces will be related to the experimental net joint moments via implicit constraints according to their polynomial-computed moment arms and the reserve actuators (i.e., F_t_ times moment arm plus *u*_*res*_). Additional constraints imposed dynamical consistency by setting pelvis residuals to zero. The u_GRF_ controls will be matched to the foot-ground contact model as implicit constraints. Raasch’s activation model will be imposed on the muscle activations via two inequality constraints based on the time constants for activation (0.015 s) and deactivation (0.06 s) of ${\dot{a}}_{MA}$ [61]. The Hill-equilibrium condition will be implicitly imposed by enforcing the muscle forces projected along the tendon to match the tendon forces. Continuality of the state variables between the end of collocation interval and the next time step will be enforced via implicit constraints. The cost function will be evaluated as the time integral between the start and end of the movement cycle, evaluated at each collocation point. The polynomials created to related joint kinematics (i.e., q and $\dot{q}$) to the MTU lengths, velocities, and moment arms will be called at each mesh point.

Best practise guidelines will be used after each simulation to assess tracking accuracy and physiological validity [83]. Tracking accuracy will be quantified via maximum and root mean squared error (RMSE) between simulated and experimental kinematics, GRFs and net joint moments. Simulated muscle activations will be qualitatively compared to the EMG in terms of timing and magnitude of the signals. Additionally, fascicle lengths and velocities, and pennation angles from the ultrasound images will be compared to the simulated MTU behaviour.

Once validated, simulated kinematics, GRFs and muscle-tendon unit forces will be used to calculate joint reaction forces using OpenSim’s Analysis Tool [59, 60].

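### The protocol ties muscle plus reserve moments to the experimental net joint moments, but elsewhere treats those as a tracking target distinct from the simulated moments that the joint reaction forces need

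*Protocol article*

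**What the plan says.** All statements are in the protocol article, under Planned data analysis, mostly in its Optimal control framework subsection.

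- **Cost function.** "Data-tracking terms will be formulated as the squared error between experimental and simulated data"; the tracked data are kinematics, ground reaction forces and net joint moments. Simulated values may therefore depart from measured ones at a price.
- **Simulated moments.** "Net joint forces and moments via inverse dynamics, and Hunt-Crossley forces will be estimated at each mesh point", from the model's own positions, velocities and accelerations, the ground-force controls and the body weight support forces.
- **Muscle constraint.** "The muscle forces will be related to the experimental net joint moments via implicit constraints", "according to their polynomial-computed moment arms and the reserve actuators". A bracket in that sentence gives the left-hand side as tendon force times moment arm plus the reserve moment.
- **Consistency constraint.** "Additional constraints imposed dynamical consistency by setting pelvis residuals to zero".
- **Accuracy check.** Maximum error and RMSE between simulated and experimental kinematics, ground forces and net joint moments are assessed after each simulation.
- **Primary outcome.** After validation, "simulated kinematics, GRFs and muscle-tendon unit forces will be used to calculate joint reaction forces". The Fig 3 caption lists the same kind of inputs: simulated kinematics, external loads and muscle-tendon forces.

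The opening of Planned data analysis says that the framework is meant to give a dynamically consistent simulation.

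**The concern.** Two different net joint moments are in play at each muscle-driven joint: one from the experiment, and one computed inside the simulation. The protocol itself treats them as different, since it penalises their difference and reports its size. The muscle constraint names the experimental one, while the joint reaction step uses motion and ground forces that belong to the simulated one. Muscle forces solved for one moment are thus combined with a skeleton that needs another.

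Joint reaction forces at hip, knee and ankle are the primary outcome, and muscle force contributes directly to them. Any mismatch between muscle moment and simulated moment therefore enters the quantity that the repeated-measures ANOVAs will compare across gravity levels.

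**Working it through.** The plan gives no figure to reproduce, because this is a question of formulation. The check is algebraic, for one muscle-driven joint.

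**Inputs from the Optimal control framework section**

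- F: tendon forces. r: their moment arms. u: reserve moment.
- M_exp: experimental net joint moment.
- M_sim: net joint moment by inverse dynamics on the simulated motion and external forces.
- e = M_exp − M_sim: the moment-tracking error.

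**Step 1: the constraint as written.** Σ(F·r) + u = M_exp.

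**Step 2: what the simulated skeleton needs.** M_sim. The cost function only penalises (M_sim − M_exp)², so e is zero only with perfect tracking.

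**Step 3: the imbalance.** Substituting M_exp = M_sim + e gives Σ(F·r) + u − M_sim = e. Muscle and reserve together miss the simulated dynamics by exactly e.

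**Step 4: do the other stated rules close it?**

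- Zero pelvis residuals close the whole-body balance at the root. They do not equate actuator moments with M_sim at hip, knee or ankle.
- The reserve sits on the same side as the muscles, against a target that is still M_exp. It changes how e is shared but leaves the sum unchanged. The muscles alone miss M_sim by M_sim − Σ(F·r) = u − e.
- The maximum error and RMSE describe e and do not remove it.

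**Step 5: the constraint against the simulated moment.** Σ(F·r) + u = M_sim. The imbalance e disappears by construction, and the muscles alone miss M_sim by u only.

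**Step 6: illustrative scale.** The documents give neither e nor r, so both are assumed here. If the reserve moment does not change and the muscles carry all of e, the muscle-force error is e / r:

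| Assumed e (N·m) | r = 0.06 m | r = 0.03 m |
|---|---|---|
| 0 | 0 N | 0 N |
| 1 | 1/0.06 = 16.7 N | 1/0.03 = 33.3 N |
| 5 | 5/0.06 = 83.3 N | 5/0.03 = 166.7 N |
| 10 | 10/0.06 = 166.7 N | 10/0.03 = 333.3 N |

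To the extent that the reserve takes up part of e, the muscle share is smaller.

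**The case against.** The strongest reply is that one adjective is being over-read. The framework aims at dynamic consistency, it computes net moments at each mesh point from the model's own state, and it zeroes the pelvis residuals. All of that fits a constraint on the simulated moments, so experimental may simply be a slip. The article is also a condensed account: it calls the reserve moment a control variable but omits it from the control vector that it prints, so the implemented equations cannot be inferred with confidence. This stands as a caution about the code. It does not remove the conflict, because the article does not leave the constraint open. It states one that disagrees with the text around it, and an analyst following the text would build the inconsistent version.

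The second reply is that safeguards limit the effect. The moment error is minimised in the objective and inspected after each simulation, activations and fascicle behaviour are compared with EMG and ultrasound, and joint reaction forces follow only after validation. These steps may keep the gap small, and they make it visible. They do not set it to zero.

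A reader might infer three stronger things that the documents do not support:

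- *That the muscle forces themselves are fixed to the experimental moments.* The constraint is on muscle plus reserve moments, so the muscle share of the gap is not determined.
- *That the relative error is worst at 0.16g.* Setting a force error against static simulated weight uses the wrong denominator, since the outcome is joint force during running, skipping, hopping and jumping. It also needs a gap that does not shrink with gravity. The Introduction reports net joint moments in walking falling in proportion to simulated gravity, and peak ground forces in submaximal hopping at reduced gravity comparable to walking and running at 1g.
- *That the gravity contrasts are biased in a known direction.* Nothing in the documents shows how the gap varies with gravity.

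**Conclusion.** The concern holds as an internal conflict. Taken literally, the muscle constraint leaves the actuator moments at hip, knee and ankle out of balance with the simulated dynamics by the moment-tracking error, which contradicts the stated aim and affects the calculation of the primary outcome. This follows from the protocol's own statements and needs no outside figure.

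Its size is unknown. It equals the tracking error, is shared in an unstated way between muscles and reserves, and may be small. The range of about 17 to 333 N for gaps of 1–10 N·m is only an illustration: it rests wholly on the assumed gap and moment arm, and on the muscles carrying everything. If the code already uses the simulated moments, the numerical effect is nil and only the text is wrong. Correction is worthwhile because the rule bears on the primary outcome and costs almost nothing to put right.

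**What to change.** Reconcile the opening of Planned data analysis with the Optimal control framework section as follows:

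1. State that tendon forces times moment arms plus reserve moments equal the **simulated** net joint moments from inverse dynamics at each mesh point.
2. Keep the experimental net joint moments only in the tracking term of the objective.
3. Report the reserve moments and the moment-tracking error alongside the joint reaction forces, so that readers can see what the muscles did not supply.

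The cost is essentially one word in the protocol and, if the code follows the present text, one constraint. If the code already uses the simulated moments, only the wording changes. Data collection, participants and sample size are unaffected.
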